#### Secondary Outcomes

Pain intensity: Assessed using the NRS-11, where scores range from 0 (no pain) to 10 (worst possible pain).Pain characteristics: Including the presence of symptoms such as itching, paresthesia and hyperalgesia.Skin lesions: Including the number of days from the initial onset of rash to healing, the largest skin lesion area.Quality of life score: Assessed using the 12-item Short-Form Health Survey (SF-12) [29].Sleep quality: Evaluated using the Pittsburgh Sleep Quality Index (PSQI) [30].Analgesic consumption: Average weekly consumption and name of rescue analgesics for each patient.Adverse events and safety assessment: Comprehensively record and analyze all treatment-related adverse events, including intra-treatment and post-treatment complications and adverse reactions.

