### Randomization and Blinding

Participants will be randomly assigned to receive either PRP treatment in combination with antiviral therapy or antiviral therapy alone in a 1:1 ratio using block randomization with a block size of 4, created with IBM SPSS Statistics 25.0. This sequence will be secured in numbered, opaque envelopes to ensure allocation concealment. Treatment efficacy and safety evaluations will be conducted by independent assessors unaware of the group assignments.

Due to the nature of the interventions, complete blinding is not possible for the doctors and patients. Therefore, this study will use blinded endpoints. The efficacy and safety evaluations will be performed by personnel not directly involved in the treatment. The evaluators who perform the assessments and the personnel conducting the statistical analysis will be blinded to the group assignments.

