#### Secondary Outcomes

For quantitative data (such as NRS-11, SF-12, and PSQI scores), the t-test or Mann–Whitney U test will be used to compare the differences between the two groups according to the data distribution characteristics. For categorical results (such as complication rate), chi-square test or Fisher's exact test will be used. All statistical analyses will use two-sided tests, with the significance level set to 0.05. For continuous repeated measurement data, such as quality of life scores at different time points after treatment, repeated measures ANOVA or mixed models will be used to analyze data for time effects and between-group effects.

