#### Data Collection and Management

*Study conduct and data collection*: This study will be conducted by specially trained research assistants responsible for collecting data from patients who meet the inclusion criteria. We will employ an Electronic Data Capture (EDC) system to collect baseline data prior to treatment, including demographic characteristics, NRS scores, SF-12, and PSQI, among others. To ensure data accuracy and confidentiality, all data will be initially recorded on paper Case Report Forms (CRFs), then verified and entered into the EDC by data management personnel.

*DSMC review:* The Data Safety Monitoring Committee (DSMC) will conduct regular reviews of the data to ensure the safe progression of the study and promptly identify any potential safety issues.

*Data access and protection:* All researchers accessing the data are required to sign a confidentiality agreement and undergo training on data protection regulations.

*Adverse events (AEs):* AEs will be meticulously documented in the CRFs and assessed by researchers for causality with the treatment. The nature, timing, duration, severity, and outcome of AEs will be recorded and evaluated by physicians. All AEs will be promptly addressed and reported to the study monitor and Institutional Review Board (IRB), especially those that are serious or life-threatening. The aim is to address any issues promptly, including halting the study if necessary.

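### The safety outcome is worded as treatment-related adverse events, which leaves the comparison open to differential attribution because only one arm has injections

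*Protocol article*

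**What the plan says.** The only definition of the safety outcome is in Outcome Assessment, Secondary Outcomes: "Comprehensively record and analyze all treatment-related adverse events". The same line counts complications during and after treatment among these events.

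Other places in the article are wider. The Methods part of the abstract and Table 1 both name adverse events with no mention of relatedness; Table 1 schedules them from week 1 to month 12. Data Collection and Management has every adverse event reported to the monitor and the IRB.

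On who judges the events, the article says two things. Randomization and Blinding states: "Treatment efficacy and safety evaluations will be conducted by independent assessors unaware of the group assignments". It also concedes that "complete blinding is not possible for the doctors and patients". Data Collection and Management states: "AEs will be meticulously documented in the CRFs and assessed by researchers for causality with the treatment". It continues: "The nature, timing, duration, severity, and outcome of AEs will be recorded and evaluated by physicians". It does not say whether these researchers and physicians are the blinded assessors.

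Under Treatment Interval and Treatment Dose, both arms receive famciclovir, and only the experimental arm also receives PRP injections, in four weekly sessions. For analysis, Statistical Analysis, Secondary Outcomes says: "For categorical results (such as complication rate), chi-square test", with Fisher's exact test as the alternative.

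**The concern.** Randomisation protects a comparison of all events that follow it. It does not protect a comparison of events chosen afterwards by a judgement that may depend on the arm. Calling an event treatment-related is such a judgement.

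Here the arms offer different things to attribute an event to. In the PRP arm, chest wall pain can be put down to a thoracic paravertebral injection, to the antiviral or to zoster. In the control arm the injection is not available as a cause. The same event may therefore count in one arm and not in the other. The opposite is also possible: a real injection effect may be put down to zoster and drop out of the count. The filter can create a difference or hide one.

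Safety is part of the stated aim, and the trial adds an invasive procedure to standard treatment, so the between-arm safety result will carry weight.

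**Working it through.** **1. Scope of the outcome against scope of the data.**

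| Place in the article | Scope |
|---|---|
| Outcome Assessment, Secondary Outcomes | treatment-related events |
| Abstract, Methods | adverse events, no limit |
| Table 1 | adverse events, week 1 to month 12, no limit |
| Data Collection and Management | all adverse events reported |

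The outcome definition is the narrow one. The data for a wider outcome will exist.

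**2. Who applies the filter.** Randomization and Blinding gives safety evaluation to blinded, independent assessors. Data Collection and Management gives causality to researchers and evaluation of the events to physicians, without stating their blinding. There are two readings:

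- If the researchers and physicians know the arm, the filter can follow the arm directly.
- If they are the blinded assessors, they are asked whether an injection caused an event without knowing whether one was given. Complications during an injection session reveal the arm by their nature.

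Neither reading gives a relatedness judgement that is both blinded and workable.

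**3. Illustration of size.** The article gives no adverse event rate and no attribution rate, so the actual size cannot be computed. The inputs are:

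- 64 patients per arm (Sample Size Calculation);
- two-sided 5% level (Statistical Analysis, Secondary Outcomes);
- assumed: a true event rate of 30% in both arms, so there is no real difference;
- assumed: the share of events called related, in three splits from wide to narrow.

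Compared rate = true rate × share called related:

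- 60% v 20%: 0.30 × 0.60 = 18%; 0.30 × 0.20 = 6%
- 50% v 25%: 0.30 × 0.50 = 15%; 0.30 × 0.25 = 7.5%
- 40% v 30%: 0.30 × 0.40 = 12%; 0.30 × 0.30 = 9%

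The rejection probability is the sum, over all pairs of event counts from 0 to 64, of the product of the two binomial probabilities wherever the test has p below 0.05. The chi-square test is taken without continuity correction.

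| Share called related, PRP v control | Compared rates | Chi-square | Fisher's exact |
|---|---|---|---|
| 60% v 20% | 18% v 6% | 56.5% | 45.8% |
| 50% v 25% | 15% v 7.5% | 26.6% | 18.4% |
| 40% v 30% | 12% v 9% | 8.5% | 4.6% |
| no filter | 30% v 30% | 5.1% | 3.1% |

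The false-positive rate is well above 5% under the two wider splits with either test. Under the narrowest split it is modestly raised with chi-square and stays below 5% with Fisher's exact test.

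**The case against.** The strongest reply is that the article says twice, in Randomization and Blinding, that safety is evaluated by people separate from treatment and blinded to group. A reader might infer from the open-label design that unblinded treating doctors judge relatedness. The documents do not say so: the researchers who assess causality are not described as unblinded, and doctors in general being unblinded does not settle who makes this judgement. That part of the objection stands. What remains is that the two sections are not reconciled and that blinded attribution to an injection is hardly feasible.

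A second reply is that the outcome line never says only. Capture and reporting cover all events, an all-event table is not precluded, and the detail of tabulation is commonly left to an analysis plan that is not shown. This stands as far as data capture is concerned. It does not reach the outcome definition, which the article does fix and which includes relatedness.

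A third reply is that no test of related events is stated outright, since the analysis section mentions complication rate only as an example. That is fair. Applying the between-group test to the safety outcome as defined is the natural reading, but it is a reading.

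Finally, the rates in the illustration are assumed, and the widest split gives the largest figure. That is also fair: the figures show what unequal attribution could do, not that it will happen.

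**Conclusion.** The point holds in a limited form. The safety outcome is narrower than the data collected, and its limit rests on a judgement that can differ by arm because only one arm has injections. The comparison is therefore open to differential attribution bias.

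A reader might go further and conclude that the comparison is biased, or biased against PRP. The documents do not support that: they give no attribution rates, the direction could be either way, and blinded safety assessors are named.

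The size is unknown. Under the assumed 30% event rate, the false-positive rate runs from about 5% (narrowest split, Fisher's exact test) to 57% (widest split, chi-square test). The matter concerns a secondary outcome and leaves the primary PHN analysis untouched. It should still be corrected, because the data are already there and the change is small.

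**What to change.** In Outcome Assessment, Secondary Outcomes, define the safety outcome as all adverse events and all serious adverse events after randomisation, compared by arm regardless of causality. Keep relatedness as a secondary description. List injection-procedure complications descriptively for the PRP arm, since they have no counterpart in the control arm.

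Reconcile Randomization and Blinding with Data Collection and Management: state who judges causality and whether that person knows the arm. The main comparison no longer depends on the answer, because an all-event count needs no causality judgement.

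The cost is a sentence or two in the outcome definition and one on the assessor. No new data are needed, since Table 1 and the data management section already provide for collecting the events. The downside is a longer table that includes events unrelated to treatment.

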### Statistical Analysis

All analyses will be conducted on an intention-to-treat (ITT) and per-protocol (PP) basis to ensure the robustness of the results.

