#### Ultrasound-Guided Thoracic Paravertebral Injection Technique

We adopted an ultrasound-guided approach for thoracic paravertebral injection, as detailed in Pu et al. [25]. The patient will be placed in the prone position to optimize access to the thoracic paravertebral space. A low-frequency convex array ultrasound probe (2–5 MHz) will be used to localize the target thoracic levels, starting in the paraspinal sagittal position and moving caudally to identify the ribs. After identifying the first rib, the probe will be moved further down the thoracic spine to locate the target segments. Typically, one to three thoracic levels will be selected based on the dermatomal distribution of ZAP, with emphasis on the most affected segments (e.g., T3, T4, and T5 for T3–T5 involvement).

Once the target level is identified, the probe will be rotated 90 degrees to achieve an axial view, allowing visualization of the transverse process, inferior articular process (IAP), and parietal pleura (PP). A 22-gauge, 80–100-mm echogenic needle will be inserted in-plane from lateral to medial, aiming for the midpoint between the IAP and PP. Doppler ultrasound will be used to avoid puncturing vascular structures. After confirming the needle placement, 3 ml of PRP will be injected at each targeted level under continuous ultrasound guidance.

Following the injection, patients will be monitored for 30 min to observe any adverse effects. A follow-up ultrasound will be performed to verify the distribution of the injectate and exclude complications such as hematomas or pleural punctures.

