#### Additional Intervention

Antiviral therapy has been widely used as the standard treatment for HZ [27]. During the treatment process, pain management will be adjusted based on pain severity and nature of the pain. For mild pain, non-opioid analgesics, such as NSAIDs, will be administered, with opioids added if the pain progresses to moderate or severe levels. Given the neuropathic component of ZAP, tricyclic antidepressants or anticonvulsants, such as gabapentin or pregabalin, may also be incorporated to enhance pain relief [28]. If the ultrasound-guided PRP injection is unsuccessful or the treatment cannot be completed for any other reason, the corresponding patient will be considered a protocol violation and must be excluded from the study.

After completing the study, the doctor will decide whether to continue auxiliary medications or other treatments based on the patient's specific condition. The dosage of medication will be adjusted according to changes in the patient's pain level, aiming to optimize therapeutic effects and improve quality of life. Treatments not mentioned in this protocol will not be permitted unless approved and standardized by the research team. All additional treatments will be documented in detail by the research assistant.

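### Per-protocol analysis of complications tends to understate PRP harm where complications stop treatment, and its agreement with ITT is no evidence of robustness

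*Protocol article*

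**What the plan says.** The opening sentence of Statistical Analysis sets one rule for everything: "All analyses will be conducted on an intention-to-treat (ITT) and per-protocol (PP) basis to ensure the robustness of the results". No separate safety set is named.

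Safety falls under that rule. The Secondary Outcomes list under Outcome Assessment includes adverse events, "including intra-treatment and post-treatment complications and adverse reactions", and the Secondary Outcomes paragraph under Statistical Analysis gives the test: "For categorical results (such as complication rate), chi-square test or Fisher's exact test will be used".

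Two sections decide who leaves the protocol-compliant group:

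- **Additional Intervention.** The trigger is "If the ultrasound-guided PRP injection is unsuccessful or the treatment cannot be completed for any other reason". The consequence is "the corresponding patient will be considered a protocol violation and must be excluded from the study".
- **Case Dropout Instructions.** A subject with a serious or key adverse event is withdrawn if the team judges it inappropriate to go on. The same section promises a last follow-up for every dropout, with effectiveness and safety analysed and the reasons recorded.

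The injection technique section provides for an ultrasound after injection to "exclude complications such as hematomas or pleural punctures". Treatment Interval and Treatment Dose plans four weekly PRP sessions, in the PRP arm only.

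**The concern.** A per-protocol set keeps patients who received treatment as planned. For a harm outcome this is a selection on something the outcome itself can cause. If a complication ends the injection course, the patient becomes a protocol violation, and both patient and event leave the PP complication rate. The non-completion rule bites mainly in the PRP arm, which alone has four invasive sessions to complete, so the expected direction is towards PRP looking safe.

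The plan gives robustness as the reason for running both sets. That reasoning does not carry over to safety: since harm is one route out of the PP set, neither agreement nor disagreement between the two results shows whether the complication rate is reliable. Safety is one of the trial's stated aims, and the plan does not say which of the two safety results governs.

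**Working it through.** **The plan's own figures.** The protocol states no complication rate and no PP set size. The only figure to reproduce is the sample size. Inputs from Sample Size Calculation: 34.8% against 10%, two-sided 5%, and 90%, which is worded as a confidence level and read here as power. With the pooled-variance formula and mean proportion 0.224:

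n = [1.960·√(2·0.224·0.776) + 1.282·√(0.348·0.652 + 0.10·0.90)]² / 0.248² = 57.3, rounded up to 58 per group, as stated.

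The plan then recruits 64 per group (58 × 1.10 = 63.8). The point below does not change the sample size. It uses 64 as the number allocated to PRP.

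**When PP is lower than ITT.** Let n be the patients allocated to PRP, a those with a complication, d the non-completers, and k the non-completers who had a complication.

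- ITT rate = a/n
- PP rate = (a − k)/(n − d)
- PP < ITT exactly when k/d > a/n

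So PP understates the rate only if complications are more frequent among those excluded than in the whole arm.

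**Illustration (assumed counts).** n = 64, a = 6, d = 6 (6/64 = 9.4%, close to the planned 10% dropout), so the PP set has 58. The control arm is assumed to have 0 of 64 complications and no exclusions. ITT rate: 6/64 = 9.4%. Here a·d/n = 36/64 = 0.56, so a single complicated non-completer (k = 1) is enough to bring PP below ITT.

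| Non-completers with a complication (k) | PP rate | Fisher p against 0/64 |
|---|---|---|
| 0 | 6/58 = 10.3% | 0.010 |
| 1 | 5/58 = 8.6% | 0.022 |
| 2 | 4/58 = 6.9% | 0.048 |
| 3 | 3/58 = 5.2% | 0.10 |
| 4 | 2/58 = 3.4% | 0.22 |
| 6 | 0/58 = 0% | 1.0 |

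The ITT comparison, 6/64 against 0/64, gives p = 0.028. The p-values should be read loosely. With equal groups the two-sided Fisher test counts both extreme tables, and with 58 against 64 it counts only one, which is why p at k = 1 is below the ITT value although the rate is lower. The pattern that matters is the loss of the signal as k rises.

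**The texts side by side.** ITT keeps every randomised patient. The dropout section keeps non-completers in a last follow-up and in the safety analysis. Additional Intervention removes them from the study. If it means removal from treatment or from the PP set, ITT still counts every event. If it is applied literally, these patients leave the ITT safety analysis too, and the calculation above applies to both sets.

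**The case against.** The strongest reply is that the safety result does not rest on PP. ITT runs alongside, dropouts are followed and their safety analysed, adverse events are documented and a monitoring committee reviews the data. This stands, and it limits the damage. It depends on the exclusion rule in Additional Intervention not being applied literally, and the protocol leaves that open.

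A second reply is that analysis sets belong to the statistical analysis plan. Formal definitions do, and their absence here is no fault. The point concerns a rule the protocol does state: all analyses on both sets.

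A reader might infer more than the documents support:

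- **That PP understates harm by construction.** It does not. The exclusion covers non-completion for any reason, the PP set is not formally defined, and the PP rate can exceed the ITT rate (10.3% against 9.4% above). Nor does the protocol say that a hematoma or pleural puncture ends the course; it only says that these are looked for.
- **That only PRP patients can be lost through harm.** That holds for failed injections. Withdrawal after a serious or key adverse event applies to both arms.
- **That ITT is equally unsuitable for safety.** ITT contains every exposed patient and every event. Its only weakness is dilution by patients allocated to PRP and never injected, and the protocol gives no number for these.
- **That the PP rate would be a third of the true rate, or zero.** Such figures come from choosing how many complications end the course.

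**Conclusion.** The point holds in a limited form. The plan's stated rule produces a per-protocol safety comparison that tends to favour PRP whenever complications are a cause of stopping, and the ITT–PP pair cannot serve as a robustness check for harm. This rests on two readings: that safety is included in all analyses, which the text supports, and that patients labelled protocol violations fall outside the PP set, which is the natural reading but is not spelled out.

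The size cannot be determined from the protocol. The range of 0% to 10.3% around an ITT rate of 9.4% depends wholly on the assumed counts. If the non-completers remain in ITT and in follow-up, the consequence is one misleading supplementary result beside a usable one. If the exclusion is literal, the main safety result is affected as well. The change is worth making because it is nearly free.

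**What to change.** 1. In Statistical Analysis, limit the per-protocol analysis to efficacy outcomes.
2. Add that safety is analysed in all randomised patients who received any study treatment, grouped by treatment received, whether or not the course was completed. Report injection complications among patients injected at least once.
3. Reconcile Additional Intervention with Case Dropout Instructions and Statistical Analysis, so that a patient who does not complete the injections may leave the PP efficacy set but stays in follow-up and in the ITT and safety analyses. This concerns data collection and analysis only; it does not touch the decision on when injections stop.

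The cost is a few sentences, with no new data and no change to the sample size. Because both groups start famciclovir at recruitment, the safety set should contain nearly the same patients as ITT. The downside for the sponsor is that reported complication rates may look slightly less favourable.

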#### Primary Outcome

A chi-square test will be used to compare the incidence of PHN between the PRP treatment group and the antiviral therapy group. Additionally, the relative risk (RR) and its 95% confidence interval will be calculated to evaluate the relative risk of PRP treatment compared to antiviral therapy.

